### Intervention

To ensure operational consistency, all patients will receive unified treatment set by the same doctor. The research assistant will add intestinal threads to the injection needles according to the respective groups. The ACE group will undergo ACE. The bilateral YingXiang (LI20), QuChi (LI11), JianJing(GB21), YinTang(GV24+), and DanZhong (CV17) points will be disinfected. Detailed positioning data are shown in Table 1 and Figure 2. The patient will assume a supine position, and acupoints will be located, marked with a marker, and disinfected with iodophor cotton swabs.

**Table 1 table1:** Location of acupoints from the World Health Organization (WHO) 2014 Standard Acupuncture Point Locations in the Western Pacific Region (SPAR) study.

Acupoint	Location
YingXiang (LI20)	On the face, next to the midpoint of the outer edge of the alar, in the nasolabial groove
QuChi (LI11)	On the lateral aspect of the elbow, at the midpoint of the line connecting LU5 with the lateral epicondyle of the humerus
DanZhon (CV17)	In the anterior thoracic region, at the same level as the fourth intercostal space, on the anterior median line
JianJing (GB21)	In the posterior region of the neck, at the midpoint of the line connecting the spinous process of the seventh cervical vertebra (C7) with the lateral end of the acromion
YinTang (EX-HN3)	At the midpoint of the line connecting the 2 medial ends of the eyebrows

**Figure 2 figure2:**
[figure not shown]
Diagram of the prescribed acupoints from the World Health Organization (WHO) 2014 Standard Acupuncture Point Locations in the Western Pacific Region (SPAR) study.

The practitioner will wear aseptic gloves, cut the absorbable surgical suture around 5 mm, and place it into the front end of the needle tube. The structure of the acupuncture needle is illustrated in Figure 3. The doctor’s left thumb and index finger will tighten the skin around the operation site, and the needle will be inserted vertically with a catgut-burying needle in their right hand at a depth of 0.5 cm. The needle will be slightly lifted to stimulate the acupoints, and after getting qi, the left hand will push the needle core inward while the right hand withdraws the needle tube outward, embedding the surgical suture in the acupoint. After the stitches are placed, the pinhole will be pressed with aseptic gauze for a while and covered with a bandage or infusion paste.

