### Randomization and Allocation Concealment

A block randomization sequence was generated by SAS software (version 9.2; SAS Institute Inc), which was performed by Guangdong Provincial Hospital of Chinese Medicine’s Key Unit of Methodology in Clinical Research. Eligible participants will be randomly assigned to either the ACE group or the sham ACE group at a ratio of 1:1. An independent researcher will prepare treatment cards, on which a serial number and one of 2 names are printed, each representing one of the 2 groups. This independent researcher will be responsible for selecting and adding intestinal thread to the injection needles according to the respective groups. Treatment allocations will be stored in password-protected files and held independently by staff of the Key Unit of Methodology in Clinical Research. While receiving the first treatment, the participants will be given sequential treatment cards from independent researchers to ensure adequate concealment. The participants will be allocated into one of 2 groups according to the name printed on their treatment card.

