**Figure 3 figure3:**
[figure not shown]
The process of acupoint catgut embedding (ACE) and the structure of the needle. a: Needles and absorbable surgical sutures. b: Specific cut-to-length. c: Insert the thread end into the needle eye. d: Insert the stylet into the needle. e: Insert the suture end into the acupoint.

Catguts will be implanted once every 7 days for a total of 28 days, and each participant will take a prescribed dose of loratadine orally every day. In the sham ACE group, participants will be placed in a supine position, and the acupoints will be located, marked with a marker, and disinfected with an iodophor cotton swab. The practitioner will wear sterile gloves and insert the needle into the skin. The doctor’s left thumb and index finger will tighten the skin around the operation site, and the needle will be inserted vertically with a catgut-burying needle in their right hand, at a depth of 0.5 cm. The needle will be slightly lifted to stimulate the acupoints, and after getting qi, the left hand will push the needle core inward. However, no absorbable surgical suture will be placed into the front end of the needle tube. After the procedure, the pinhole will be pressed with aseptic gauze for a while and covered with a bandage or infusion paste. This procedure will also be conducted once a week for 4 consecutive weeks. Each participant will take a prescribed dose of loratadine orally every day. Participants from both groups will be instructed to stop symptomatic RMs during the 1-week run-in and treatment periods. However, they will be allowed to take RMs if needed during the follow-up period. The use of RMs will need to be documented in the participants’ diaries.

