### Outcome Measurement

For an evaluation of the primary and secondary outcome measures, the participants are required to complete 2 questionnaires, the Total Ocular Symptom Score (TOSS) and the Total Nasal Symptom Score (TNSS) [19]. These questionnaires will be completed at the beginning of each of the 4 treatment sessions (from week 2 to week 5) and in weeks 8, 12, and 16 during each follow-up session. During the follow-up process, the participants need to independently record their Rhinitis Control Assessment Test (RCAT) scores weekly [20]. In addition, the participants will be asked to complete diaries throughout the trial. The primary outcome is the recurrence rate 3 months after discontinuation. Once the treatment-effective participants discontinue the medication (RCAT score less than 21 points), they will immediately enter the follow-up period. If a relapse occurs, the relapse time will be promptly recorded, and the follow-up will conclude. Otherwise, the participants will continue to be monitored until 3 months after discontinuation of medication. RCAT is one of the most commonly used rhinitis control scales, and its reliability, validity, and responsiveness have been widely verified [21,22]. A score of 21 corresponds to the validated RCAT score of 25, which determines the controlled state of rhinitis. When RACT ≤21, it indicates an uncontrolled state of AR and the starting point for treatment [23]. RCAT is a simple self-rating scale that allows patients to assess their AR control at home and helps assess the success of long-term repeated treatment interventions [20,24]. TNSS evaluates 4 nasal symptoms: nasal obstruction, sneezing, rhinorrhea, and nasal itch. The symptoms are self-assessed and recorded by participants using a 5-point scale (0=no symptoms; 1=mild symptoms; 2=moderate symptoms; 3=severe symptoms; 4=very severe symptoms) [23]. TNSS scores range from 0 to 16, with low scores indicating lighter nasal symptoms. TOSS assesses eye symptoms, including redness, itchiness, and tearing. Each symptom is assessed on a scale between 0 and 3 (absent to most severe), with a total score from 0 to 9 [19,25]. The score represents an average for both eyes. The secondary outcomes include (1) changes in TNSS and TOSS score from baseline to weeks 8, 12, and 16; (2) response to interventions, defined as participants with a change in TNSS score of ≥0.5 from baseline; (3) and serum levels of tumor necrosis factor-alpha (TNF-α), IFN-γ, IL-4, IL-17, and IgE, measured by enzyme-linked immunosorbent assay according to the manufacturer's protocol (Bio-Techne).

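### The article names three different roles for loading the thread, and its ACE script has a cutting-and-loading step that the sham script neither contains nor mimics

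*Protocol article*

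**What the plan says.** Three places in the Methods assign the loading of the thread.

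- Randomization and Allocation Concealment: "This independent researcher will be responsible for selecting and adding intestinal thread to the injection needles according to the respective groups".
- Intervention, opening paragraph: "The research assistant will add intestinal threads to the injection needles according to the respective groups".
- Intervention, ACE procedure (text after Figure 2): the practitioner puts on gloves and is to "cut the absorbable surgical suture around 5 mm, and place it into the front end of the needle tube".

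The ACE description starts with "The patient will assume a supine position", followed by marking and disinfection of the points. The practitioner's cutting and loading comes after that in the text.

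The sham description (Intervention, text after Figure 3) has the same positioning, marking and disinfection, and then says "The practitioner will wear sterile gloves and insert the needle into the skin". Later it states the intended difference: "However, no absorbable surgical suture will be placed into the front end of the needle tube".

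The Blinding section says that participants are blinded, that researchers and acupuncturists are not, and that outcome assessors are. After each session participants report whether they think they received ACE and rate their certainty from 0 to 10. On the RCAT, Outcome Measurement says "RCAT is a simple self-rating scale that allows patients to assess their AR control at home". The same section has participants complete the TNSS and TOSS.

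**The concern.** In this trial the patient is the person whose blinding counts most. The treating staff know the allocation by design, and the patient supplies every symptom score. Blinding the outcome assessors and the statistician does little for a score that the patient writes down.

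The sham has to look and feel like ACE from the treatment couch. The printed scripts do not secure this, because one arm has a manual step with thread that the other lacks. If that step happens where the patient can watch, an ACE patient could learn the allocation. Expectation could then affect the recurrence comparison as well as the nasal and ocular scores. According to the Sample Size Calculation section, patients with ineffective treatment are left out of the recurrence assessment. Self-rated response could therefore also affect who is assessed for the primary outcome.

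**Working it through.** No figure in the plan is at issue, so there is nothing to recompute. The check is a comparison of texts.

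**Step 1. The two scripts, in text order.**

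| Step | ACE | Sham |
|---|---|---|
| Position | Supine | Supine |
| Points | Marked, disinfected | Marked, disinfected |
| Gloves | Yes | Yes |
| Suture cut and put in the tube by the practitioner | Yes | Absent, and nothing mimed |
| Insertion | Vertical, 0.5 cm | Vertical, 0.5 cm |
| Lift, getting qi | Yes | Yes |
| End of manoeuvre | Core pushed, tube withdrawn | Core pushed; withdrawal not written |
| Pinhole | Pressed and covered | Pressed and covered |

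The sham text follows the ACE text closely, down to hand positions and dressing. Against that background the missing cutting-and-loading step stands out as a difference between the arms.

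**Step 2. Who loads the needle.** The three assignments are the independent researcher, the research assistant and the practitioner. The first two could be one person under two titles. The third cannot be squared with either, because a needle that arrives already loaded according to group does not need loading by the practitioner.

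**Step 3. What each reading implies for blinding.**

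- Needles loaded beforehand and elsewhere, by the independent researcher or the assistant: the loading difference is invisible to the patient and blinding is not threatened on this point.
- Needles loaded by either of them in the treatment room: whether the patient notices depends on arrangements that the article does not describe.
- Needles loaded by the practitioner as the ACE procedure is written: the ACE session has an extra action between gloving and insertion, after the patient is in place, and the sham session does not.

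The article does not choose among these. It mentions no screen, no blindfold, no mimed loading and no separate place of preparation.

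**Step 4. Which outcomes are exposed.** RCAT, TNSS and TOSS are completed by the participant. The serum markers are laboratory measurements, but they are secondary and are not symptom outcomes.

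**Step 5. What the existing safeguard does.** The questionnaire after each session can show that patients in the two arms guess differently. It cannot restore blinding for a patient who has already worked out the allocation.

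**The case against.** The strongest reply is that the article states twice that someone other than the practitioner loads the needle. If that is the practice, the ACE paragraph is only loose drafting. The article is also a condensed account. It refers to standard operating procedures in the Blinding section and to a written protocol and procedure documents in Quality Control. Trays, screens and the place of preparation belong naturally in those documents. This stands in part: silence about sight lines would not be a finding by itself. It does not remove the contradiction, because the article itself prints a practitioner's script that conflicts with its other two statements.

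Four stronger readings are tempting, and the document does not support them.

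- A reader might infer that patients can see which arm they are in. No sentence says that cutting and loading is done at the bedside or in view. Text order suggests it but does not establish it.
- A reader might infer that a patient who sees no thread loaded knows that the arm is sham. In a parallel design each patient experiences one script, so not seeing thread tells the patient little unless they know that active needles are loaded in view. The more plausible route is an ACE patient who does see the thread.
- A reader might count tube withdrawal as a second visible difference, since the ACE script has the practitioner "push the needle core inward while the right hand withdraws the needle tube outward" and the sham script stops at pushing the core. The sham needle is inserted and the pinhole is then pressed, so it must come out too. This is probably abbreviation.
- A reader might attach a number of percentage points of bias, or count every implant as a visible loading step. The count assumes that every loading is seen. The bias would need the share of patients who recognise their allocation and the resulting shift in self-rated recurrence, and the document gives neither.

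**Conclusion.** The point holds in a limited form. The article contradicts itself on who loads the thread. On the wording of its ACE procedure, the sham lacks a step that the active arm has, and no statement places needle preparation out of the patient's sight. If that wording is followed in view of the patient, participant blinding is at risk for the symptom outcomes, including the primary one. The risk rests on two conditions that the document leaves open: that the practitioner, or someone else in the room, does the loading, and that the patient can observe it. If needles are already prepared elsewhere, only the text is at fault.

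The size of any bias cannot be derived from the document. The Sample Size Calculation section takes a 5% lower recurrence rate as the clinically relevant difference, so the trial aims at a small effect on a self-rated scale. That is a reason to secure the blinding, but it is no evidence that the blinding fails. This is a worthwhile, inexpensive improvement to make; it does not show that the trial is compromised.

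**What to change.** Reconcile the three statements in the Randomization and Allocation Concealment and Intervention sections:

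1. Name one role for needle preparation. The independent researcher already described under Randomization and Allocation Concealment is the obvious choice. State that this person prepares every needle, threaded or empty, out of the patient's sight.
2. Remove cutting and loading from the practitioner's script.
3. Print one practitioner script for both arms, from gloving to dressing and including tube withdrawal, and state that only the content of the needle differs.
4. Keep the questionnaire after each session as the check that this works.

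Recruitment is under way. If the change alters practice as well as wording, record its date at each site, so that blinding responses before and after it can be told apart.

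The cost is a small change to the operating procedure and brief retraining at the three sites. The article does not say whether the independent researcher is present at each site. Where that person is not, someone must be assigned to the role locally.

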**Figure 3 figure3:**
[figure not shown]
The process of acupoint catgut embedding (ACE) and the structure of the needle. a: Needles and absorbable surgical sutures. b: Specific cut-to-length. c: Insert the thread end into the needle eye. d: Insert the stylet into the needle. e: Insert the suture end into the acupoint.

Catguts will be implanted once every 7 days for a total of 28 days, and each participant will take a prescribed dose of loratadine orally every day. In the sham ACE group, participants will be placed in a supine position, and the acupoints will be located, marked with a marker, and disinfected with an iodophor cotton swab. The practitioner will wear sterile gloves and insert the needle into the skin. The doctor’s left thumb and index finger will tighten the skin around the operation site, and the needle will be inserted vertically with a catgut-burying needle in their right hand, at a depth of 0.5 cm. The needle will be slightly lifted to stimulate the acupoints, and after getting qi, the left hand will push the needle core inward. However, no absorbable surgical suture will be placed into the front end of the needle tube. After the procedure, the pinhole will be pressed with aseptic gauze for a while and covered with a bandage or infusion paste. This procedure will also be conducted once a week for 4 consecutive weeks. Each participant will take a prescribed dose of loratadine orally every day. Participants from both groups will be instructed to stop symptomatic RMs during the 1-week run-in and treatment periods. However, they will be allowed to take RMs if needed during the follow-up period. The use of RMs will need to be documented in the participants’ diaries.

### Outcome Measurement

For an evaluation of the primary and secondary outcome measures, the participants are required to complete 2 questionnaires, the Total Ocular Symptom Score (TOSS) and the Total Nasal Symptom Score (TNSS) [19]. These questionnaires will be completed at the beginning of each of the 4 treatment sessions (from week 2 to week 5) and in weeks 8, 12, and 16 during each follow-up session. During the follow-up process, the participants need to independently record their Rhinitis Control Assessment Test (RCAT) scores weekly [20]. In addition, the participants will be asked to complete diaries throughout the trial. The primary outcome is the recurrence rate 3 months after discontinuation. Once the treatment-effective participants discontinue the medication (RCAT score less than 21 points), they will immediately enter the follow-up period. If a relapse occurs, the relapse time will be promptly recorded, and the follow-up will conclude. Otherwise, the participants will continue to be monitored until 3 months after discontinuation of medication. RCAT is one of the most commonly used rhinitis control scales, and its reliability, validity, and responsiveness have been widely verified [21,22]. A score of 21 corresponds to the validated RCAT score of 25, which determines the controlled state of rhinitis. When RACT ≤21, it indicates an uncontrolled state of AR and the starting point for treatment [23]. RCAT is a simple self-rating scale that allows patients to assess their AR control at home and helps assess the success of long-term repeated treatment interventions [20,24]. TNSS evaluates 4 nasal symptoms: nasal obstruction, sneezing, rhinorrhea, and nasal itch. The symptoms are self-assessed and recorded by participants using a 5-point scale (0=no symptoms; 1=mild symptoms; 2=moderate symptoms; 3=severe symptoms; 4=very severe symptoms) [23]. TNSS scores range from 0 to 16, with low scores indicating lighter nasal symptoms. TOSS assesses eye symptoms, including redness, itchiness, and tearing. Each symptom is assessed on a scale between 0 and 3 (absent to most severe), with a total score from 0 to 9 [19,25]. The score represents an average for both eyes. The secondary outcomes include (1) changes in TNSS and TOSS score from baseline to weeks 8, 12, and 16; (2) response to interventions, defined as participants with a change in TNSS score of ≥0.5 from baseline; (3) and serum levels of tumor necrosis factor-alpha (TNF-α), IFN-γ, IL-4, IL-17, and IgE, measured by enzyme-linked immunosorbent assay according to the manufacturer's protocol (Bio-Techne).

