### Statistical Analyses

Intentional therapeutic analysis will be adopted, with missing values estimated using the last observation carried forward method. Mean and SD (for continuous variables that obey normal distribution), median and quartile (for continuous variables that do not obey normal distribution), and frequency and percentage (for classified variables) will be used for the statistical description. According to the numerical characteristics of the variables, quantitative data such as age, height, and weight of the 2 groups will be compared using a *t* test or the Wilcoxon rank sum test. The chi-square test or Fisher exact probability method will be used to compare qualitative variables, such as sex and nationality between the 2 groups. Cox regression analysis will be carried out with recurrence outcome and time of first recurrence as dependent variables, and the differences in survival curves between both groups will be compared. SPSS software (version 23.0; IBM Corp) will be used for statistical analysis. A 2-sided test will be used for all statistical inferences, and *P*<.05 will be considered statistically significant.

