### Sample Size Calculation

Our preliminary study [28] indicated that the 3-month recurrence rate of the ACE group should be at least 5% lower than that of the Sham ACE group to be clinically significant. Using α=0.025 (unilateral), β=0.2, △=5%, and K=1, the sample size was estimated based on the comparison of two sample rates in the optimization test. The sample size in each group was calculated to be 52. Since the effectiveness of any treatment was not 100%, patients with ineffective treatment in this study could not be included in the assessment of recurrence, so the loss of follow-up rate in this study was 20%, which amounted to 126 cases. The \following equation is used to calculate the sample size, which refers to the estimated number of patients to be enrolled in the study:

[figure not shown]

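### The RCAT cut-off printed for entry to recurrence follow-up (below 21) falls wholly inside the range the same section calls uncontrolled (21 or below)

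*Protocol article*

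**What the plan says.** Four parts of the protocol article bear on this.

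- **Entry to the primary-outcome follow-up** (Outcome Measurement): "Once the treatment-effective participants discontinue the medication (RCAT score less than 21 points), they will immediately enter the follow-up period".
- **Relapse** (next sentence): "If a relapse occurs, the relapse time will be promptly recorded, and the follow-up will conclude". No RCAT value is attached to it.
- **Meaning of the scale** (same section): "When RACT ≤21, it indicates an uncontrolled state of AR and the starting point for treatment" (RACT is a misprint for RCAT). Higher scores therefore mean better control. The preceding sentence equates 21 with a validated score of 25 that marks control.
- **Timing of RCAT** (same section): "During the follow-up process, the participants need to independently record their Rhinitis Control Assessment Test (RCAT) scores weekly". The text mentions no RCAT at the end of treatment.

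The Sample Size Calculation section restricts the assessable population: "patients with ineffective treatment in this study could not be included in the assessment of recurrence". The Statistical Analyses section names the model: "Cox regression analysis will be carried out with recurrence outcome and time of first recurrence as dependent variables".

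**The concern.** The only number printed beside the effectively treated patients points the wrong way. Read literally, a patient joins the recurrence follow-up as a treatment success while in the state that the section treats as the trigger for starting treatment. A patient who is actually controlled does not qualify.

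This threshold matters more than most. The Introduction makes reduction of recurrence the focus of the primary objective. Because ineffectively treated patients are left out of the recurrence assessment, the line between effective and ineffective decides who is in the risk set for the primary outcome and for the Cox model. If recurrence means a return to RCAT 21 or below, every patient admitted by the printed rule has already recurred at time zero, and time to first recurrence has no meaning for them.

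Timing adds to the concern. Recruitment is under way, and the Blinding section says that researchers and acupuncturists know the allocations. A threshold settled after scores have been seen would be open to challenge, even with blinded assessors and a blinded statistician.

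**Working it through.** **1. Compare the two rules.** Both are in Outcome Measurement and both use the 21 cut-off. Controlled is taken as the complement of the printed uncontrolled range.

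| RCAT score | Printed entry condition (<21) | Printed state (≤21 uncontrolled) | Do the rules agree? |
|---|---|---|---|
| below 21 | admitted as effective | uncontrolled | no |
| exactly 21 | not admitted | uncontrolled | yes |
| above 21 | not admitted | controlled | no |

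The set {RCAT < 21} is contained in {RCAT ≤ 21}. Its overlap with {RCAT > 21} is empty. The rules give the same label only at 21 and opposite labels at every other score. This does not depend on the range of the scale.

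**2. Look for a reading that removes the conflict.**

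- If the parenthesis qualifies stopping the medication, patients stop treatment in the state that calls for starting it.
- If the inequality is reversed, entry becomes a score above 21 (or at least 21), and relapse has no printed cut-off.
- If the parenthesis is a relapse criterion that belongs one sentence later, relapse is a score below 21, and effective treatment has no printed cut-off. A weekly score of exactly 21 would then be uncontrolled by the section's own definition but not a relapse.
- The link between 21 and 25 does not help, because both rules are stated at 21.

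**3. Size against the planned numbers.** Inputs from Sample Size Calculation: "The sample size in each group was calculated to be 52" and "so the loss of follow-up rate in this study was 20%, which amounted to 126 cases".

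- Reproducing the total: 52 × 1.20 = 62.4, rounded up to 63 per group; 2 × 63 = 126, as printed.
- Planned assessable: 2 × 52 = 104.
- Allowance for ineffective treatment or loss: 126 − 104 = 22, or 11 per group on an even split.

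Suppose the allowance holds and effective means controlled. Then the 104 all score above 21 and none meets the printed condition. Only patients among the remaining 22 could meet it, and those lost to follow-up would not contribute. The literal rule therefore admits at most 22 where the plan needs 104.

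**The case against.** The strongest reply is that the parenthesis was never an entry rule. It follows the words about stopping medication, the next sentence concerns relapse and lacks a number, and RCAT recording is described only for follow-up, which suits an instrument for detecting relapse. On that view, below 21 is a misplaced relapse cut-off and the conflict with 21 or below shrinks to one score. This is a plausible account of how the error arose. It does not make the printed sentence correct, and it leaves effective treatment without any threshold.

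Four smaller points deserve an answer.

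- **Another response criterion exists.** The section defines response as a change in TNSS of at least 0.5 from baseline. That is a separate secondary outcome, and nothing links it to entry into the recurrence follow-up.
- **The 22-versus-104 comparison is not realistic.** This is fair as a prediction: the allowance is a planning figure that mixes non-response with dropout, and a site would probably infer the intended direction. The comparison shows only what the text says if followed literally.
- **The 21-to-25 sentence could put 21 on the controlled side.** It is ambiguous, but it affects only the score of 21. The explicit statement puts 21 among the uncontrolled scores.
- **Figure 1 may show an end-of-treatment RCAT.** Its legend lists RCAT, but the figure was not available for this review. The request is therefore to confirm the timing; no omission is asserted.

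**Conclusion.** The concern holds. The only numeric condition printed for entry to the primary-outcome follow-up admits no controlled score and contradicts the definition of control in the same section. Nothing else in the article reconciles the two. The first inequality is spelled out in words, so it is not a garbled symbol, and this is a misstatement, not a detail left to a fuller document.

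The general direction of the intended rule can be inferred. The exact rule cannot: the two plausible repairs fix different halves of the definition, and the candidate relapse cut-offs disagree at 21.

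The contradiction itself needs no assumption. The figure of at most 22 against a planned 104 assumes that the sample-size allowance holds and that effective means controlled. The statement that every literal entrant has already recurred at time zero assumes that recurrence means a return to RCAT 21 or below, which the article does not say. This must be fixed because it defines the primary outcome. The sample size is unaffected.

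**What to change.** Amend the protocol, with a dated record, before any outcome is classified:

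- **Effective treatment (entry to recurrence follow-up):** RCAT above 21 at the end of treatment.
- **Recurrence:** first weekly follow-up RCAT of 21 or below.
- If a different relapse cut-off such as below 21 is intended, state it separately and make it consistent with the definition of uncontrolled.
- Confirm that RCAT is completed at the end of treatment.

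The cost is a one-line amendment and a note to the three sites while recruitment continues. At most it adds one self-rated questionnaire per participant, if an end-of-treatment RCAT is not already collected.
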